## Abstract

**Background:** Sleep-Disordered Breathing (SDB) varies from habitual snoring to partial or complete obstruction of the upper airway and can be found in up to 10% of children. SDB can significantly affect children's wellbeing, as it can cause growth disorders, educational and behavioral problems, and even life-threatening conditions, such as cardiorespiratory failure. Adenotonsillectomy represents the primary treatment for pediatric SDB where adeno-tonsillar hypertrophy is indicated. For those with craniofacial anomalies, or for whom adenotonsillectomy or other treatment modalities have failed, or surgery is contra-indicated, mandibular advancement splints (MAS) may represent a viable treatment option. Whilst the efficacy of these appliances has been consistently demonstrated in adults, there is little information about their effectiveness in children.

**Aims:** To determine the efficacy of mandibular advancement appliances for the management of SDB and related health problems in children.

**Methods/design:** The study will be designed as a single-blind crossover randomized controlled trial with administration of both an “Active MAS” (Twin-block) and a “Sham MAS.” Eligible participants will be children aged 8–12 years whose parents report they snore ≥3 nights per week. Sixteen children will enter the full study after confirming other inclusion criteria, particularly Skeletal class I or class II confirmed by lateral cephalometric radiograph. Each child will be randomly assigned to either a treatment sequence starting with the Active or the Sham MAS. Participants will wear the appliances for 3 weeks separated by a 2-week washout period. For each participant, home-based polysomnographic data will be collected four times; once before and once after each treatment period. The Apnea Hypopnea Index (AHI) will represent the main outcome variable. Secondary outcomes will include, snoring frequency, masseter muscle activity, sleep symptoms, quality of life, daytime sleepiness, children behavior, and nocturnal enuresis. In addition, blood samples will be collected to assess growth hormone changes.

**Trial registration:** This study was registered in the Australian New Zealand Clinical Trials Registry (ANZCTR): [ACTRN12614001013651].

## Introduction

The health impact of sleep-disordered breathing (SDB), particularly, obstructive sleep apnea (OSA) has been increasingly recognized in both adults and children (Marcus, 2001; Casale et al., 2009). The prevalence of OSA in children varies from 1 to 4% (Rosen et al., 2003; Bixler et al., 2009; Bonuck et al., 2011), while most authors report a 10% prevalence of habitual snoring in children (Lumeng and Chervin, 2008). SDB has been associated with growth disorders (Marcus et al., 1994), daytime sleepiness (Li and Lee, 2009), educational and behavioral problems (Blunden et al., 2000; Galland et al., 2015), and nocturnal enuresis (Stone et al., 2008). In the most severe cases, OSA may have life-threatening consequences like cardiorespiratory failure, which can lead to death (Ross et al., 1987; Lavie, 2004).

Enlarged adenoids and tonsils are the most common etiology of OSA in children. Obesity during childhood represents another important risk factor for OSA (Horner et al., 1989; Gozal and Kheirandish-Gozal, 2009). Craniofacial anomalies are also associated with changes in airway morphology and respiratory problems (McNamara, 1981). These anomalies, basically, include maxillary and mandibular retrognathia, increased facial height, decreased facial width, increased overjet, and palatal crossbite (Lofstrand-Tidestrom et al., 1999; Cakirer et al., 2001; Kawashima et al., 2002; Li et al., 2002; Ozdemir et al., 2004; Juliano et al., 2009; Pirila-Parkkinen et al., 2009; Flores-Mir et al., 2013; Katyal et al., 2013).

Polysomnography (PSG) is considered the gold standard for SDB diagnosis (Casale et al., 2009), and the apnea hypopnea index (AHI) is the main outcome to aid diagnosis. AHI is defined as the number of apnea and hypopnea events recorded per hour of sleep. A pediatric OSA event, relying on PSG, is defined as absence of airflow for two respiratory cycles (2 breaths) with continued chest wall and abdominal wall movement (Berry et al., 2012). Whereas, obstructive hypopnea is defined as a decrease in nasal flow ≥30% (lasting at least 2 breaths) with a corresponding decrease in oxygen saturation ≥3% and/or arousal (Berry et al., 2012).

Full PSG is costly to perform in sleep laboratory, and scoring sleep stages is time consuming (Collop et al., 2007). Consequently, over the last decades, there has been increased interest in cost-effective methods of diagnosing SDB within the home setting using portable monitoring devices (Bridevaux et al., 2007; Polese et al., 2010). Type III home PSG, also referred to as abbreviated PSG without electonecephalogram (EEG), electrooculogram (EOG), and electromyogram (EMG), has been used in the majority of the published studies on home testing of SDB in children; this abbreviated PSG, is more suitable for use in children, it is less time-consuming, and it is easier to set up and score (Tan et al., 2015).

The first line and the most common treatment for pediatric OSA is adenotonsillectomy (Li and Lee, 2009; Marcus et al., 2012). Although significant improvements in the AHI are observed following adenotonsillectomy, full resolution of OSA (AHI ≤ 1) occurs only in 27–60% of cases (Friedman et al., 2009; Bhattacharjee et al., 2010). Adenotonsillectomy is also associated with risk of postoperative complications beyond the anesthetic and surgical procedures. For example, OSA children show a significantly higher risk of respiratory compromise, defined as intermittent or continuous oxygen saturation of 70% or less, and/or hypercapnia, requiring intervention after surgery (McColley et al., 1992; Gross et al., 2006). Children with obesity, severe OSA, or craniofacial abnormalities may require more protracted inpatient care and/or intensive care unit observation (Leong and Davis, 2007; Isaacson, 2014). Studies have reported an accelerated mandibular ramus growth and improved facial morphology after adenotonsillectomy in pediatric OSA patients (Agren et al., 1998). This improvement may be due to normalization in growth hormone (GH) serum levels, also to a change of tongue and cheek posture (Woodside et al., 1991). However, this growth acceleration is not sufficient to correct the malocclusion and the underlying skeletal discrepancy often requires subsequent dentofacial growth modification treatment (Peltomäki, 2007).

Continuous positive air pressure (CPAP) is the primary treatment option for adult OSA (Casale et al., 2009). CPAP is also advocated for severe pediatric SDB (Agren et al., 1998), or for persistent OSA after adenotonsillectomy, but it is generally not well tolerated by children (Marcus et al., 2012). Adherence to CPAP treatment in children is a major problem, with rates of only 30–70% (O'Donnell et al., 2006; Uong et al., 2007). From a biomechanical stand-point, there are anecdotal reports of potential facial growth disturbances from long-term use of CPAP due to the elastic strap which maintains the mask, as it may apply a restraining force on the growing maxilla (Conley, 2011).

Oral appliances have also been widely used for the treatment of OSA, particularly in adults (Villa et al., 2002; Ferguson et al., 2006; Casale et al., 2009). These appliances increase the posterior oropharyngeal airway and reduce upper airway collapsibility by holding the mandible in a protruded position during sleep; furthermore, the device may trigger stretch receptors, which in turn activate the airway supporting muscles (Casale et al., 2009). Previous studies have shown that oral appliances are better tolerated than CPAP treatment (Ferguson et al., 2006) because of improved comfort, quietness, and portability. Mandibular advancement appliances are the most common type of oral appliances used in the treatment of SDB in adults, but their use in children is less common, with little information about their efficacy (Ferguson et al., 2006). The few studies on the subject suffer from important methodological flaws, making it difficult to reach a definitive conclusion about the efficacy of MAS appliances in children with SDB (Villa et al., 2002; Cozza et al., 2004; Carvalho et al., 2007; Huynh et al., 2015; Nazarali et al., 2015).

## Objectives

Aims of the study are:(1) to test the short-term efficacy of MAS in the treatment of children with SDB; and (2) to assess the effect of MAS treatment on quality of life, behavior, growth hormone levels, and nocturnal enuresis in SDB children.

## Materials and methods

### Study design

This study will be carried out as a single-blind crossover randomized controlled trial. Each participant will wear two appliances consisting of an active MAS and non-active MAS (Sham MAS). Each appliance will be worn for a 3-week treatment period, which will be separated by a 2-week washout period. A similar study design and treatment time have been used in previous studies comparing the efficacy of MAS to nasal CPAP treatment in adults (Ferguson et al., 1996, 1997).

This study will be conducted in the Discipline of Orthodontics, School of Dentistry University of Otago, New Zealand. Ethical approval has been granted by the Human Ethics Committee at University of Otago [H14/054], and New Zealand Health Research South Ethics Committee- Southern District Health Board [01050]. The research has also been approved by Ngāi Tahu Research Consultation Committee (Research consultation with Māori).

### Participants

#### Sample size estimation

A reduction of 50% in AHI is generally considered clinically relevant (Ferguson et al., 2006). This change corresponds to a large effect size (Cohen's *d* = 1.5). To detect this effect size, and setting α error to 0.05 and β error to 0.20 (one-tail test) using a repeated-measurement design, we have estimated that at least 13 participants are needed. We will recruit 16 children to account for possible dropouts.

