Randomized clinical trials represent the gold standard for the evaluation of therapeutic effectiveness (Mills et al., 2007) therefore, unlike the previous studies, it is expected the current study protocol will provide new robust and reliable information about the possible efficacy of MAS for the management of SDB in children. The crossover design will allow each participant to act as his/her own control, thus increasing the power of the study. This study will also systematically address efficacy of MAS on other important health outcomes related to SDB, such as quality of life, neurobehavioral functioning, and growth hormone changes; outcomes that have not been widely addressed in previous intervention studies investigating pediatric snoring or OSA (Huynh et al., 2015)

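### The figure of 13 children does not follow from d = 1.5, one-tailed 0.05 and 80% power in an ordinary within-child comparison, which needs about 5 (4 to 8); the mismatch is conservative

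*Protocol article*

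**What the plan says.** The whole justification of the size is in the Protocol article, Sample size estimation. It starts from clinical relevance: "A reduction of 50% in AHI is generally considered clinically relevant". It then standardises that reduction: "This change corresponds to a large effect size", given as Cohen's d = 1.5. With α = 0.05, β = 0.20 and a one-tailed test, it concludes: "using a repeated-measurement design, we have estimated that at least 13 participants are needed". Dropout is added afterwards: "We will recruit 16 children to account for possible dropouts".

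Two other places fix the comparison as within-child. Study design says "Each participant will wear two appliances consisting of an active MAS and non-active MAS (Sham MAS". The Discussion says "The crossover design will allow each participant to act as his/her own control, thus increasing the power of the study". The Discussion also says that the size was based on AHI alone.

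The article does not say which SD scales d, what within-child correlation was assumed, or which contrast was powered.

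**The concern.** A standardised effect of 1.5 is very large, and a crossover uses children efficiently. Together they should give a single-digit number. Thirteen at exactly 80% power looks too many, as if the gain from the crossover were missing or a smaller effect had been used.

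The obvious innocent explanations do not apply. The dropout allowance comes after the 13, and secondary outcomes played no part in the estimate.

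What is at stake is the meaning of the trial's only power statement. If the effect is right, the power is far above 80%. If the number and the power are right, the effect behind them is about half of 1.5 read as a within-child standardised difference, and the step from a 50% fall in AHI to d = 1.5 played no part in the size. A reader of the results could not tell what size of effect the trial was built to detect.

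**Working it through.** **Inputs from Sample size estimation:** d = 1.5; one-tailed α = 0.05; power 0.80; repeated measurements; stated result 13. **Assumed, because not given:** the within-child correlation ρ, taken from 0 to 0.7.

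**Formula.** For n children with one active and one sham value each, the test statistic is noncentral t with noncentrality d_z·√n. The degrees of freedom are n − 1 (paired test) or n − 2 (crossover with a period term). Here d_z is the mean active-minus-sham difference divided by the SD of the within-child differences.

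**Step 1. d = 1.5 read as d_z.** At n = 5 the noncentrality is 1.5 × √5 = 3.35.
- n = 4: power 0.735
- n = 5: power 0.862 (0.811 with a period term)
- n = 13: power 0.9997

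The requirement is 5.

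**Step 2. d = 1.5 on the between-child SD.** Then d_z = 1.5/√(2(1 − ρ)).

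| ρ (assumed) | d_z | n, paired | n, with period term |
|---|---|---|---|
| 0 | 1.06 | 8 | 8 |
| 0.25 | 1.22 | 6 | 7 |
| 0.5 | 1.50 | 5 | 5 |
| 0.7 | 1.94 | 4 | 5 |

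At the least favourable of these (ρ = 0), power with 13 is 0.975, or 0.973 with a period term.

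**Step 3. Sidedness.** A two-sided 0.05 test needs 6 at d_z = 1.5 (7 with a period term) and 10 at ρ = 0. Sidedness does not explain the gap.

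**Step 4. What d_z does 13 correspond to?** At 80% power:

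| Completers | One-tailed 0.05 | Two-sided 0.05 |
|---|---|---|
| 13 | 0.73 | 0.85 |
| 16 | 0.65 | 0.75 |

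The one-tailed value for 13 is about half of 1.5 (0.73/1.5 = 0.49). In the two-value model of Step 2, d_z = 0.75 would need ρ = 1 − (1.5/0.75)²/2 = −1.

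**Step 5. Routes that do give 13.**
- Two independent groups of 6 and 7, d = 1.5, one-tailed, noncentrality 1.5·√(n₁n₂/(n₁ + n₂)): power 0.811. Groups of 6 + 6 give 0.780; equal groups need 7 + 7 = 14 (0.841).
- Paired test with d_z = 0.75: 0.817 at n = 13, 0.785 at n = 12.
- A between-groups repeated-measures F-test with f = 0.75, ρ = 0.5 and α = 0.05: N = 13.
- Change from baseline on active minus change from baseline on sham, using all four recordings. With d on the between-child SD and equal correlation, the SD of the contrast is 2·SD·√(1 − ρ), so d_z = 0.75/√(1 − ρ). At ρ = 0, n = 13 (0.817; 0.813 with a period term). At ρ = 0.05, n = 12, or 13 with a period term. At ρ = 0.25, n = 10; at ρ = 0.5, n = 8.

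**Step 6. The move from 13 to 16** is consistent with a dropout allowance of 3/16 = 18.75%. Nothing is wrong there.

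**The case against.** The best defence is that the trial takes four sleep recordings, one before and one after each treatment period, so two values per child may be the wrong model. The double-difference contrast in the last route of Step 5 keeps every stated input and yields 13 when ρ is about 0 to 0.05. This stands as a matter of arithmetic. It rules out saying that no non-negative correlation can produce 13, and it shows that the range of 4 to 8 belongs to the active-versus-sham model only. Under the four-recording contrast, power with 13 runs from 0.82 at ρ = 0 to 0.975 at ρ = 0.5.

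It does not rescue the statement. It requires AHI in the same child to be essentially uncorrelated between nights, whereas the Discussion relies on each child being his or her own control to raise power. With moderate correlation the same contrast needs 10 or 8. The article does not say that this contrast was powered.

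A reader might also infer that the authors ignored the crossover and sized a parallel-group trial, or that they halved the effect. The documents support neither diagnosis. An equal-group calculation gives 14, other routes also reach 13, and no working is shown.

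Finally, an article may leave the SD and correlation to the full protocol, and their absence alone would not be a finding. Here, however, effect, α, power, sidedness, design and result are stated together, and under the ordinary comparison they do not agree.

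**Conclusion.** The point holds in a limited form. For the ordinary within-child active-versus-sham comparison, the stated inputs need 5 children, or about 4 to 8 if d is on the between-child SD and ρ lies between 0.7 and 0. With 13 completers the power is 0.97 or more. Of the routes tried, those that reach 13 change a stated input or add an implausible correlation, and the one actually used is not shown.

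A reader might take this to mean that the trial is underpowered. It does not: if d = 1.5 is right, the error is conservative and the trial has more children than its inputs require. No enrolment or analysis decision has to change. This should be fixed because it is the only power statement on the primary outcome, but it is not a must-fix.

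The conclusion rests on the assumed range of ρ and on the t-test model. It does not depend on which route the authors took.

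**What to change.** Keep 16 children and rewrite the sentence on the effect size and the number needed:
- Define the effect as d_z, the mean active-minus-sham difference in AHI divided by the SD of the within-child differences.
- State what the size detects at 80% power: with the stated one-tailed 0.05, d_z = 0.73 for 13 completers and 0.65 for 16. If the test is to be two-sided, the values are 0.85 and 0.75. Whether it should be two-sided is a separate question that this check does not settle.
- Remove d = 1.5, or keep it and give the contrast, SD and within-child correlation that turn it into 13.

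The cost is one rewritten sentence, with no change to enrolment.

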#### Recruitment

We will advertise in local newspapers to invite children who live in Dunedin city/New Zealand, to participate in the study according to the following eligibility criteria: age 8–12 years; parental report of snoring three nights or more per week.

Eligible patients should meet the following selection criteria:

A score for the Pediatric Sleep Questionnaire (PSQ) ≥0.33 (Chervin et al., 2000); class II or class I incisor relationships; Skeletal maxillomandibular relations of class I or class II which will be confirmed by lateral cephalometric radiograph (ANB angle and Wit's appraisal; Steiner, 1959; Jacobson, 1975).Exclusion criteria include severe OSA defined as an AHI >10 (Association ASA, 2013); craniofacial syndromes and genetic syndromes; neuromuscular diseases; or Angle class III incisor relationships; previous orthodontic treatment.Patients diagnosed with severe OSA will be referred to a Medical Specialist.

**Figure 1 F1:**
[figure not shown]
**Appliances tested in a pilot study to identify the most suitable appliance design to be used in the main study. (A)** Traditional Twin-block: Removable upper and lower acrylic plates, each plate has matching pieces to encourage the lower jaw to slide forward, bilateral hooks were added to insert vertical elastics. **(B)** Metallic fastener Twin-block: Removable upper and lower vacuum formed plates and a metallic fastener (TAP) is used to hook the upper and the lower plates enabling the mandible to be advanced forward. **(C)** Clear elastic Twin-block: Removable upper and lower vacuum formed plates with matching pieces to encourage the lower jaw to slide forward, bilateral plastic hooks were added to accommodate vertical elastics. **(D)** Sham Twin-block: Removable upper and lower vacuum formed plates, without any lower jaw advancing device.

As discomfort affects adaptation and acceptance (Sergl and Zentner, 1998; Idris et al., 2012), this was evaluated in a pilot study using two assessment methods: the participant was firstly asked to report how comfortable was each appliance immediately after insertion into the oral cavity in compare to the other appliances. The four appliances were presented in pairs to compare each appliance to the remaining three (a total of 12 pairs were generated to avoid confounding caused by sequence of appliances application); the participant was instructed to insert an appliance into the mouth and he was asked to move the mandible to the right and left, front and back, and then to swallow, then to repeat the same to another appliance; after that the participant was asked to indicate which of the two appliances was more comfortable to wear. The second method aimed to assess acceptance after wearing the appliance for 2 h while awake and during one night sleep. One night appliance-free was allowed as washout period between two sequentially-tested appliances. Discomfort was assessed by using a 100-mm visual analog scale (VAS) with words (worse than I can imagine; better than I can imagine) anchored at the left and right end of the scale, corresponding to worse discomfort and best comfort, respectively. The participant rated the discomfort intensity by putting a vertical slash on the line that best represented the intensity of discomfort. The higher the VAS score the better the appliance acceptance. Two separate VAS scores were collected after both the awake and asleep wearing periods.

Retention was tested using both a subjective and an objective assessment. Subjective assessment was made by asking the participant (1) if the appliance was held in the mouth the whole night, (2) if the upper and lower splints were fitting well to the teeth, and (3) if the upper and lower splints stay attached to each other. Response options were yes/no.

Passive and active retention were also objectively tested by two independent examiners (GI, MF) by checking whether the appliance was stable in-mouth upon, (1) maximum jaw opening and, (2) direct pulling of the examiner.

Since the traditional Twin-block appliance showed the best retention and acceptance this was chosen as the study protocol intervention. Additional arguments in support of this decision were:

It is easy to titrate and can also be used to expand the upper arch.It includes metal clasps to increase retention as required.It is very popular amongst orthodontists and has been extensively tested in previous research.It has a low failure rate and is well tolerated by children (Morris et al., 1998).It can be used for facial growth modification in patients with skeletal class II jaw relationship.

#### Twin-block design (active MAS)

This consists of two removable upper and lower plates; each plate has matching pieces which encourage the lower jaw to posture or slide forward as the teeth come together (Figure 2) (Clark, 1988). Hooks will be added to the Twin-block bilaterally to insert vertical elastics. These elastics will hold the mouth closed during sleep and the mandible postured in a forward position (Barnes et al., 2004). The construction bite of the appliance will be determined using the George Gauge™(George, 1992), which allows an accurate determination and registration of the mandibular advancement. The bite registration will be taken for all participants by advancing the mandible 75% of the maximum protruded position of the jaw with minimum bite opening.

